### Frequency and plans for auditing trial conduct {23}

On-site monitoring will comprise controlling presence and completeness of the research files and the informed consent forms, source data checks will be performed as described in the monitoring plan. Every participating center will be visited at least once every year.

Monitoring in the Leiden University Medical Center, the coordinating site, will be executed by internal monitors of the LUMC according to the monitor plan. Independent monitoring of participating sites will be arranged by the coordinating investigator and principal investigator.

### Plans for communicating important protocol amendments to relevant parties (e.g., trial participants, ethical committees) {25}

A substantial amendment is defined as an amendment to the terms of the ethical reviewing board application, or to the protocol or any other supporting documentation, that is likely to affect to a significant degree:
The safety or physical or mental integrity of the subjects of the trial;The scientific value of the trial;The conduct or management of the trial; orThe quality or safety of any intervention used in the trial.

All substantial amendments will be notified to the ethical reviewing board and to the competent authority.

### Dissemination plans {31a}

The study protocol and analysis plan will be published before start of the study on trialregister.nl (trial number: 7376). The results of the study will be presented to (inter-) national scientific journals, professional societies, and guideline committees. We will submit analyses to scientific journals in the field of Intensive Care medicine as well as anesthesiology, since both ICU physicians and anesthesiologists apply ventilation in the ICU setting. The results of this study will be disclosed unreservedly according to the Central Committee on Research Involving Human Subjects (CCMO) statement on publication policy (http://www.ccmo.nl/attachments/files/ccmo-statement-publicatiebeleid-3-02-en.pdf). Material for public dissemination will be submitted to the sponsor for review prior to submission for publication. Each study site will provide one co-author, when at least ten subjects have been included. If more than one hundred subjects have been included or reasonable efforts have been made to reach this number the study site will provide two co-authors. The co-authors will be determined in accordance with general accepted academic standards for authorship. Prior to submission, co-authors will look through the manuscript. No parties involved have veto right.

## Discussion

The ICONIC study is a randomized clinical trial that is sufficiently powered to investigate whether a difference in outcome exists between mechanically ventilated ICU patients targeted at conservative or conventional oxygenation. Our aim is to replicate the study that was conducted by Girardis et al., in order to see if we would come to equivocal conclusions. After starting the ICONIC trial, the evidence of the previously mentioned Italian trial [16] and before mentioned studies resulted in clinical practice guidelines that emphasized a more conservative approach of oxygen therapy [6, 22–24, 26]. This encouraged the start of several other randomized trials, including the ICU-ROX, LOCO_2_, the HOT-ICU, and the present trial.

The ICU-ROX investigators compared conservative oxygen therapy (targeting SpO_2_ of 90–96%) to usual care (SpO_2_ > 90%) in 1000 adults undergoing mechanical ventilation in Australia and New Zealand. Conservative oxygen therapy did not improve ventilator-free days or survival in mechanically ventilated adults. However, the interventions compared were conservative oxygen therapy and usual care targeting SpO_2_, and the actual difference in achieved SpO_2_ values between the two groups was minimal. Possibly the chosen target ranges were too close and did not allow sufficient discrimination, reducing the chance to detect any difference in endpoint.

The LOCO_2_ trial planned to randomize 850 French ARDS patients to conservative (target PaO_2_ 55–70 mmHg; target SpO_2_ 88–92%) or liberal oxygen therapy (target PaO_2_ 90–105 mmHg; target SpO_2_ ≥ 96%). However, the trial was stopped prematurely after enrolling 205 patients because of safety concerns due to ischemic events occurring in the conservative group.

Lastly, the most recent published trial from the HOT-ICU group randomized 2928 mechanically ventilated ICU patients to a PaO_2_ of either 60 mmHg or a PaO_2_ of 90 mmHg. No difference in death within 90 days was found. A limitation of this study was that possibly two “normoxia” targets were compared and that there was limited contrast in the applied intervention.

The most recent trials do not support the previously found benefits of conservative oxygen use [16]. Potential explanation for the negative findings in later trials is the lack of contrast between the oxygenation targets (intervention) in both study groups. To add, no truly hyperoxic targets were included in the negative trials. In the literature, hyperoxia or higher targets are either defined as an PaO_2_ of > 100 mmHg, an PaO_2_ > 150 mmHg or even an PaO_2_ of > 300 mmHg [31–35]. In the study by Girardis that did show benefit in the lower oxygenation group, the PaO_2_ target in the control group was up to 150 mmHg, thus more hyperoxic than the oxygenation targets in the negative RCTs.

In order to build on previously published, results we hope to answer questions that remained unanswered in existing literature. Therefore, one of the strengths of the ICONIC is that we chose targets that are further apart, namely 55–80 mmHg vs 110–150 mmHg. To add, to maximize generalizability, we plan to not only focus on ARDS but include patients with a variety of conditions. Due to evidence of ischemia in the conservative group in the LOCO_2_ trial, we will monitor occurrence of ischemic events (cardiac, intestinal, cerebral, and peripheral) closely.

A limitation of this study can be the difficulty for patients to reach their target range. The ability to reach a higher target range highly depends on the lung function and underlying disease. Therefore, it might be possible that a patient is randomized to the higher group but due to underlying condition or clinical deterioration is not able to reach the higher target. We attempted to minimize this risk by excluding patients with ARDS and a P/F ratio < 20, but we can unfortunately not anticipate on the risk of future clinical deterioration. Also patients with healthy lungs that are randomized in the lower oxygenation group might easily reach an SpO_2_ of above 80 mmHg with the slightest additional oxygen. For this reason, patients with an expected duration of ventilation of less than 24 h are also excluded. Another limitation of this study could be that we focus on the whole ICU population instead of subgroups. Suggestions in literature have been made that some subgroups might benefit from a higher or lower oxygenation strategy, but a recent mini-review by Demiselle et al. shows that when pooling the data from different subgroups that still no “optimal” oxygenation target for subgroups can be chosen [36]. Also groups in which a specific oxygen target is proven to be beneficial, for example in COPD patients, were excluded from the study.

In conclusion, the ICONIC study is an investigator-initiated international randomized clinical trial aiming to answer the question how to target oxygen therapy by investigating whether a difference in outcome exists between mechanically ventilated ICU patients targeted at conservative or conventional oxygenation.

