### Sample size {14}

Based on an expected mortality in the control group of 24% (source: Dutch NICE foundation; NICE online [27]), we will include 1512 patients to detect an absolute difference in mortality of 6% (2-sided, alpha 0.05, power 80%, similar allocation of subjects to each group and corrected for 4% dropouts). The choice of 6% was motivated by the difference of 8% found in a previous trial [16] comparing conventional to conservative oxygenation targets and what could be considered clinically acceptable.

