## Data collection and management

### Plans for assessment and collection of outcomes {18a}

Only data needed to assess primary and secondary objectives will be collected in electronic case report forms and extraction from the patient registry systems. Data will be regularly checked on quality, errors, and outliers and corrected if possible.

Two questionnaires are used for the follow-up of subjects from the Netherlands:
EQ-5D [28, 29]A self-developed questionnaire assessing patient opinion and experience of the consent procedure of research in the emergency setting, which is a modified and translated version of the questionnaire used in a previous trial [30].

Subjects will receive these questionnaires per mail or e-mail.

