#### Secondary outcome

Secondary endpoints that fall under the category of continuous normally distributed variables will be expressed as frequencies and percentages. Differences between groups in continuous normally distributed variables will be expressed by their means and standard deviations or when not normally distributed, as medians and their interquartile ranges. Secondary endpoints that fall under the category of categorical variables will be expressed as frequencies and percentages. Differences between groups in continuous variables will be analyzed with Student’s *t* test or, if continuous data is not normally distributed, the Mann-Whitney *U* test will be used. Categorical variables will be compared with the chi-squared test or Fisher’s exact test, as appropriate. Statistical significance is considered to be at a *p*-value < 0.05 with a two-sided test. When appropriate, statistical uncertainty will be expressed by 95% confidence levels. In addition to the unadjusted *p*-values for secondary outcomes, a procedure will be applied to control for multiple testing.

All statistical analyses will be performed with the R language and environment for statistical computing (R Foundation for Statistical Computing, Vienna, Austria).

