### Composition of the data monitoring committee, its role and reporting structure {21a}

An independent Data Safety and Monitoring Board (DSMB) watches over the ethics of conducting the study in accordance with the Declaration of Helsinki and monitors safety parameters and the overall conduct of the study. The DSMB is composed of three independent individuals. The DSMB will meet at least yearly. No competing interests were reported by the DSMB.

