### Adverse event reporting and harms {22}

Adverse events (AE) are defined as any undesirable experience occurring to a subject during the study, whether or not considered related to the trial procedure and intervention strategies. Since this is a low-risk study in critically ill patients, comparing two currently used PaO_2_ targets, additional undesirable events related to the study protocol are not anticipated. Therefore, we will only register serious adverse events (SAEs) and will not record AEs.

Because this is a study in critically ill patients, SAEs are expected to occur frequently. Therefore, the following SAEs are not considered untoward in this population and will not be treated as SAE:
Death not related to the study interventionInfectionsBleedingOrgan failure

The following events occurring during ICU admission will be treated and registered as SAE:
PaO_2_ ≤ 5 kPa (37.5 mmHg)Ischemic events (limbs, cerebral, myocardial, intestinal)In-hospital cardiac arrest (IHCA)SpO_2_ < 80% for longer than 10 min (not explained by technical failure)Death possibly related to the study intervention

The site investigator will report all SAEs to the leading investigator without undue delay after obtaining knowledge of the events.

The sponsor or lead investigator will report the SAEs through the web portal to the accredited ethical reviewing board that approved the protocol, within 7 days of first knowledge for SAEs that result in death or are life threatening followed by a period of maximum of 8 days to complete the initial preliminary report. All other SAEs will be reported within a period of maximum 15 days after the sponsor has first knowledge of the serious adverse events.

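### Intestinal ischaemia is registered as an SAE and named in the monitoring promise, but is missing from the ischaemic-events endpoint that is compared between arms

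*Protocol article*

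**What the plan says.** The protocol article lists the components of ischaemic events three times.

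- **Outcomes {12}**, as a secondary endpoint: cardiac, neurological and peripheral. No time window is attached.
- **Adverse event reporting and harms {22}**, as an SAE: "Ischemic events (limbs, cerebral, myocardial, intestinal", where the list ends. The lead-in sets the window: "The following events occurring during ICU admission will be treated and registered as SAE".
- **Discussion**, as a commitment: "we will monitor occurrence of ischemic events (cardiac, intestinal, cerebral, and peripheral) closely". The reason given is an earlier trial of low oxygenation targets, stopped early because of "safety concerns due to ischemic events occurring in the conservative group".

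The abstract says only ischaemic events and does not settle which list applies. For the analysis, the Secondary outcome section states that "Categorical variables will be compared with the chi-squared test or Fisher’s exact test, as appropriate". The article describes no between-arm comparison of SAEs. The DSMB "monitors safety parameters and the overall conduct of the study", and its numerical stopping guideline under Interim analyses {21b} concerns mortality only.

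**The concern.** Ischaemia is the harm of low targets that the authors themselves single out, and the Discussion names the gut among the sites to watch. The endpoint that would carry the between-arm test does not list it. Applied as written, an intestinal event is recorded as an SAE and adds nothing to the ischaemic-events comparison. The trial could then report no difference in ischaemic events while one of the sites it promised to watch differs between arms.

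This is not detail left to a fuller document. The Outcomes section gives a closed list in brackets, and that list disagrees with two others in the same article.

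**Working it through.** **1. The three lists side by side**

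| Site | Outcomes {12} | Adverse events {22} | Discussion |
|---|---|---|---|
| Heart | cardiac | myocardial | cardiac |
| Brain | neurological | cerebral | cerebral |
| Limbs / periphery | peripheral | limbs | peripheral |
| Gut | not listed | intestinal | intestinal |

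Three rows match one to one. The gut is absent only from the endpoint. The Discussion sets intestinal beside peripheral as separate items, so on the one occasion when both words appear together, peripheral does not include the gut. The SAE list has limbs and intestinal as separate items, which fits that reading but does not use the word peripheral.

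**2. Number per arm**

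The Sample size section gives 1512 patients, 1:1 allocation, 24% against 18% mortality, two-sided 0.05, 80% power and 4% dropout. The pooled-variance formula for two proportions gives 723 per arm, so 1446 in total, and 1446 / 0.96 = 1507 after rounding up. The stated 1512 is reproduced to within 5 patients. Evaluable patients per arm: 1512 × 0.96 / 2 = 725.76, taken as 726. This figure is used only for the illustration below.

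**3. What the omission could cost (assumed rates)**

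The article gives no ischaemic-event rates, so all rates here are assumptions: other ischaemia 2%, 3% or 5% and equal in both arms; intestinal ischaemia 0.5% in the conventional arm; component rates additive (no patient with two types); test at an unadjusted two-sided 0.05.

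With d = p₁ − p₀, p̄ the mean of p₀ and p₁, and n = 726:

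- se₀ = √(2 p̄(1−p̄)/n)
- se₁ = √([p₀(1−p₀) + p₁(1−p₁)]/n)
- power = Φ((d − 1.96 se₀)/se₁) + Φ((−d − 1.96 se₀)/se₁)

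Worked example, other ischaemia 3%, intestinal 0.5% versus 2.5%: p₀ = 0.035, p₁ = 0.055, p̄ = 0.045. Then se₀ = √(2 × 0.045 × 0.955 / 726) = 0.01088 and se₁ = √((0.033775 + 0.051975)/726) = 0.01087. The first term is Φ((0.02 − 0.02133)/0.01087) = Φ(−0.12) = 0.45; the second is negligible.

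| Intestinal, conventional vs conservative | Excess events (726 × d) | Power, four components (other ischaemia 5% to 2%) | Power, intestinal alone |
|---|---|---|---|
| 0.5% vs 1.0% | 3.6 | 7–9% | 20% |
| 0.5% vs 1.5% | 7.3 | 13–20% | 48% |
| 0.5% vs 2.5% | 14.5 | 34–55% | 88% |
| 0.5% vs 3.5% | 21.8 | 61–83% | 98% |

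In every row the three-component endpoint rejects at 5%, because by assumption nothing it counts differs between arms. For a doubling or tripling of intestinal ischaemia, the four-component composite would also usually show no difference. It passes 50% power only for excesses of about five-fold or more. The intestinal component alone does better in every row.

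**4. Windows**

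SAEs are registered during ICU admission. The endpoint has no stated window. If it runs beyond ICU discharge, the SAE records would not capture intestinal events over the same period as the other components. The data-collection section also says that "Only data needed to assess primary and secondary objectives will be collected in electronic case report forms", so intestinal events outside the SAE route are not clearly collected while they remain outside the endpoint.

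**The case against.** **Peripheral may be meant broadly.** The Outcomes section uses a three-way scheme and defines none of its terms, and the SAE list never uses the word peripheral. One Discussion sentence makes the narrow reading the more likely one but does not prove it. This stands as a limit on certainty: a reader might infer that peripheral cannot include the gut, and the article does not go that far. It does not remove the conflict, because the word would then carry two meanings in one article.

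**Intestinal events would not go unseen.** A reader might infer that an intestinal excess would be invisible, or that the monitoring promise is broken. Neither is supported. These events are registered as SAEs during ICU admission, reported to the leading investigator and then to the ethical reviewing board, and fall within the DSMB's safety remit. What is lost is their place in the planned comparison of ischaemic events.

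**The power illustration can be made to look large.** Showing only five- to seven-fold excesses, with no effect at any other site, would flatter the case for the composite. That objection is right, and it is why the smaller effects are in the table. The article also plans a multiplicity procedure for secondary outcomes, so power at adjusted levels would be lower.

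**The change is not free.** Recruitment began in November 2018, care is open-label, and outcome assessors are unblinded. Redefining a secondary endpoint mid-trial may need to go through the amendment process. This stands, and it supports making the change while the data analysts are still blinded, or choosing by-arm tabulation instead.

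**Conclusion.** The inconsistency is real. The endpoint list conflicts with both the SAE list and the monitoring promise and, read literally, leaves intestinal ischaemia out of the between-arm comparison that bears on the harm the authors single out.

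The size cannot be fixed from the article. Under the assumptions above, the four-component composite has anywhere from 7% to 83% power, so adding the component to the composite is a modest gain unless the excess is large. Component-level reporting carries most of the benefit.

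It would be tempting to say that no new data are needed because the events are already SAEs. The article does not establish this, because the SAE window is ICU admission and the endpoint window is unstated. The 28-day mortality endpoint, the sample size and the mortality-based stopping guideline are unaffected. This is a point that should be corrected, not one that threatens the trial's main conclusion.

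**What to change.** - Use one component list (cardiac, neurological, intestinal, peripheral) in Outcomes {12}, Adverse event reporting and harms {22} and the Discussion.
- Report each component by arm, with counts and confidence intervals, beside the composite.
- State one ascertainment window for all components. If it extends past ICU discharge, say how intestinal events after discharge are found.
- Make and date the change before the blinded data analysts see allocation, so that it cannot look data-driven.
- If leaving the gut out was deliberate, say so, define peripheral, and commit to tabulating intestinal SAEs by arm.

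**Cost.** The wording change is one line in the outcome definition plus matching terms elsewhere. It may need notification as an amendment. If the window is longer than ICU stay, some further data collection is needed. Adding a component that does not differ between arms dilutes the composite slightly, which the component table makes visible. The by-arm tabulation alone avoids redefining the endpoint and meets most of the safety concern.

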## Trial status

Protocol version number: Version 11, 13 February 2020

Date recruitment began: 19 November 2018

Approximate date when recruitment will be completed: 1 January 2022

## Data Availability

Upon reasonable request, the dataset and statistical code will be made available by the principal investigator.

## Abbreviations

AE: Adverse event
ARDS: Acute respiratory distress syndrome
APACHE: Acute Physiology And Chronic Health Evaluation
CCMO: Central Committee on Research Involving Human Subjects; in Dutch: Centrale Commissie Mensgebonden Onderzoek
COPD: Chronic obstructive pulmonary disease
DSMB: Data Safety Monitoring Board
(e)CRF: (Electronic) Case Report Form
FiO_2_: Fraction of inspired oxygen
Hb: Hemoglobin
ICU: Intensive care unit
IHCA: In-hospital cardiac arrest
LOS: Length of stay
LUMC: Leiden University Medical Centre
NICE: National Intensive Care Evaluation
NWO: Dutch research council
PaO_2_: Partial pressure of arterial oxygen
PBW: Predicted body weight
PEEP: Positive end-expiratory pressure
PROVE: PROtective VEntilation
RCT: Randomized clinical trial
SAE: Serious adverse event
SOFA: Sequential Organ Failure Assessment
SpO_2_: Oxyhemoglobin saturation
VA-ECMO: Veno-arterial extracorporeal membrane oxygenation
WMO: Medical Research Involving Human Subjects Act (in Dutch: Wet Medisch-wetenschappelijk Onderzoek met Mensen)
